#### Plans to promote participant retention and complete follow-up {18b}

The trial participant will be followed up by telephone or WeChat during treatment and 6 months after treatment.

### Data management {19}

All data will be kept confidential. Data will be stored electronically with encryption, allowing only authoring investigators to enter data. A participant identifier code for the data will be used so that data will not have the participant’s name associated with it. A separate key file connecting the participant name and participant identifier code will be created and stored in a secured location where only the principal investigator has direct access to the list. Participant identifier codes will be used for all data entry and data analyses.

### Confidentiality {27}

All manual data related to the trial will be safely stored in the restricted access location. Participant identification information, written informed consent, and other relevant sensitive data documents in the trial will not be exposed to anyone outside the research team.

### Plans for collection, laboratory evaluation, and storage of biological specimens for genetic or molecular analysis in this trial/future use {33}

Blood and semen samples will be collected and tested by the laboratory department of Guilin People’s Hospital in accordance with the standard testing procedures, and biological samples will not be preserved. No genetic studies are currently planned.

## Statistical methods

### Statistical methods for primary and secondary outcomes {20a}

Data analysis will be performed using IBM SPSS Statistics for Windows, version 24 (IBM Corp., Armonk, NY, USA). Compliance of variables with normal distribution will be analyzed by the Shapiro-Wilk test and homogeneity of variance by Levene’s test. Continuous variables will be expressed as mean with standard deviation (mean ± SD) or median (25 to 75%). Categorical variables will be expressed as numbers with percentages. Continuous data that are normally distributed and homogeneous in variance will be analyzed with one-way analysis of variance, and if the result is statistically significant, multiple comparisons will be performed with Bonferroni correction. Continuous data that do not obey normal distribution or have unequal variance will be analyzed with the Kruskal-Wallis test, if the result is statistically significant, then the Wilcoxon signed-rank test, with a Holm-Bonferroni method correction for multiple comparisons. Within groups before and after the intervention will be analyzed by paired-samples *t*-test for normally distributed variables and Wilcoxon signed-rank test for non-normally distributed variables. Categorical data will be analyzed using Pearson’s chi-square test or Fisher’s exact test. The level of significance will be set to *p* < 0.05.

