### Outcomes {12}

The primary outcome is the change of semen parameters (mainly progressive motility sperm) compared between the study groups at baseline and after 3 months of oral medication. Semen samples will be collected in sterile containers by masturbation after 2–7 days of abstinence. A semen analysis will be performed within 60 min after ejaculation and liquefaction using semen quality analyzer, and the semen volume, PH, sperm concentration, total motion, progressive motility (PR), and normal morphology will be measured according to the WHO laboratory manual for the examination and processing of human semen (5th edition) [25].

As secondary outcomes, the following will be measured at baseline and after 3 months of treatment: (1) Sex hormones, including follicle-stimulating hormone (FSH), luteinizing hormone (LH), estradiol (E2), and testosterone (T), will be determined by electrochemiluminescence using fasting blood. (2) Testicular volume will be calculated using Lambert’s formula (length × height × width × 0.71) [26]. (3) Sperm DNA fragment index (DFI) will be detected by flow cytometry-assisted sperm chromatin structure analysis (SCSA), seminal plasma malondialdehyde (MDA) levels will be detected by means of the tiobarbituric acid method, and seminal plasma total antioxidant capacity (TAC) will be detected by ferric-reducing antioxidant power (FRAP) assay method. (4) The pregnancy rate will be assessed during the 6-month follow-up after the completion of the trial.

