### Sample size {14}

Sample size estimation uses a completely random design to compare multiple sample means. The target sample size was estimated on PR sperm (as the primary outcome of this trial) using the PASS 2021 version 21.0.3 (NCSS, LLC, Kaysville, UT, USA). The number of samples considering the type I error *α* = 0.05 and the type II error *β* = 0.20 with 80% test power. According to a previous study [23], and a retrospective analysis of our data center in the past 2 years, changes in PR sperm mean value in the surgical observation group was 12.05, and the standard deviation was 3.96; changes in PR sperm mean value in the surgical control group was 6.56, and the standard deviation was 8.90; changes of PR sperm mean value in the non-surgical observation group was 4.15, and the standard deviation was 8.68; changes of PR sperm mean value in the non-surgical control group was 1.42, and the standard deviation was 7.60. After calculation, the sample size required for each group was 16 people. To reduce error, we slightly expanded the target sample size and estimated a dropout rate of 20%. The sample size will be practically 20 patients per group, and we will consider a total of 80.

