### Data collection and management

#### Plans for assessment and collection of outcomes {18a}

Data will be collected at three time points: (T0) pre-treatment (baseline) records—baseline parameters, sperm quality, sex hormones, testicular volume, sperm DFI, seminal plasma MDA, and TAC; (T2) 3 months post-treatment—sperm quality, sex hormones, testicular volume, DFI, seminal plasma MDA and TAC, and adverse event; and (T3) 6 months post-treatment—pregnancy rate.

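### Change in progressive motility is compared between groups without baseline as a covariate; ANCOVA would usually be more precise at almost no cost

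*Protocol article*

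**What the plan says.** The outcomes section ({12}) opens thus: "The primary outcome is the change of semen parameters (mainly progressive motility sperm) compared between the study groups at baseline and after 3 months". Sample size {14} is built on means and SDs of changes in PR, for example "changes in PR sperm mean value in the surgical observation group was 12.05, and the standard deviation was 3.96", so the natural reading is that the change score is the variable tested.

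Statistical methods {20a} names the between-group tests. If assumptions hold, "Continuous data that are normally distributed and homogeneous in variance will be analyzed with one-way analysis of variance", and after a significant result "multiple comparisons will be performed with Bonferroni correction". Otherwise, "Continuous data that do not obey normal distribution or have unequal variance will be analyzed with the Kruskal-Wallis test". No covariate is mentioned in either branch or anywhere else in the article.

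Plans for assessment and collection of outcomes {18a} lists sperm quality among the baseline data: "T0) pre-treatment (baseline) records—baseline parameters, sperm quality, sex hormones". Sequence generation {16a} describes blocked 1:1:1:1 allocation and mentions no stratification.

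**The concern.** A change score is 3-month PR minus exactly 1 times baseline PR. The coefficient that minimises residual variance is the within-group regression slope of 3-month PR on baseline, which equals r when the two visits have the same SD and is then below 1. Forcing it to 1 over-corrects: an arm that happens to start low is credited with some improvement that it would have shown anyway. With about 20 men per arm and no stratification on PR, chance differences at baseline are to be expected, and part of each one is carried into the comparison of changes.

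What is at stake is precision, chiefly for the pairwise ALA versus vitamin E comparisons. These bear on whether ALA does better than a traditional antioxidant, and they have much less power than the omnibus test. The method is written into the article, so it is a stated choice and not a detail left to an analysis plan.

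**Working it through.** **1. The protocol's own figure.** Inputs from Sample size {14}: mean changes 12.05, 6.56, 4.15 and 1.42; SDs 3.96, 8.90, 8.68 and 7.60; "the type I error *α* = 0.05 and the type II error *β* = 0.20 with 80% test power". The grand mean is 6.045, and the squared deviations sum to 36.06 + 0.27 + 3.59 + 21.39 = 61.31. For the four-group F test, λ = n × 61.31 / SD². The common SD used is not stated. The largest, 8.90, gives λ = 16 × 61.31 / 79.21 = 12.38 and power 82.6% at n = 16, against 79.7% at n = 15. So 16 per group is reproduced, and 16 / 0.8 = 20. At 20 per group the power is 91.1%.

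**2. Variance of ANCOVA relative to the change score.** Let s be the baseline SD, k the ratio of the 3-month SD to the baseline SD, and r the within-group correlation.

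- Var(change) = s²(1 + k² − 2rk)
- Residual variance in ANCOVA = s²k²(1 − r²)

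With k = 1 the ratio is (1 − r²) / [2(1 − r)] = (1 + r)/2. The protocol gives neither r nor k, so both are varied:

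| k | r = 0.3 | r = 0.5 | r = 0.7 |
|---|---|---|---|
| 1.0 | 0.65 | 0.75 | 0.85 |
| 1.2 | 0.76 | 0.87 | 0.97 |
| 1.4 | 0.84 | 0.94 | 1.00 |

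The ratio never exceeds 1. It reaches 1 when the regression slope rk is 1.

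**3. Effect of a chance imbalance.** Given a baseline difference D between two arms, the expected error of the change-score comparison is −(1 − rk)D, or −(1 − r)D at k = 1. To size it from the protocol's own SD of change, put k = 1 and SD of change = 8.90. Then s = 8.90/√[2(1 − r)], one standard error of D at 20 per arm is s√(2/20), and a one-standard-error imbalance shifts the comparison by 8.90 × 0.316 × √[(1 − r)/2] = 1.7, 1.4 or 1.1 PR points at r = 0.3, 0.5 or 0.7. The planned non-surgical difference is 4.15 − 1.42 = 2.73.

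A simulation of 20,000 two-arm trials (20 per arm, assumed SD 10, r = 0.5) confirms the pattern. Over all trials the mean error of the change score is about 0. Among trials with an imbalance above one standard error it is −2.4, against −0.05 for ANCOVA.

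**4. Power for the tests actually planned.** Assumptions: k = 1, 20 per group, and one error degree of freedom lost to the covariate. The omnibus test uses SD 8.90 × √[(1 + r)/2] = 7.18, 7.71 or 8.21. Each pairwise contrast uses its own two SDs and a two-sided noncentral t.

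- Surgical: difference 12.05 − 6.56 = 5.49; SE = √[(3.96² + 8.90²)/20] = 2.18.
- Non-surgical: difference 2.73; SE = √[(8.68² + 7.60²)/20] = 2.58.
- Adjusted SE = SE × √[(1 + r)/2].

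| Test | Change score | ANCOVA, r = 0.3 / 0.5 / 0.7 |
|---|---|---|
| Omnibus | 91% | 99 / 97 / 95% |
| Surgical, α = 0.05 | 69% | 86 / 81 / 76% |
| Surgical, α = 0.05/6 = 0.0083 | 41% | 63 / 55 / 49% |
| Non-surgical, α = 0.05 | 18% | 25 / 22 / 20% |

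The 0.0083 level assumes that all six pairs are tested; the 0.05 rows are an uncorrected reference. The pairwise figures ignore the requirement that the omnibus test be significant first.

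**The case against.** Much of the case on the other side stands.

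- A reader might infer that the planned comparison is biased or invalid. It is not. Randomisation makes the change-score contrast unbiased on average, and regression to the mean acts on all four arms alike. An error appears only conditionally on an imbalance that has occurred, and then only the fraction 1 − r of it when the SDs are equal.
- A reader might infer that the baseline is thrown away. A change score uses it, with a fixed coefficient instead of an estimated one.
- A reader might infer that the trial misses its power target without adjustment. On the protocol's inputs the omnibus test has about 83% power at 16 per group and 91% at 20. Nor does the protocol plan a pooled ALA main effect, so a power gain for such a test would not describe the stated analysis.
- Entry requires abnormal semen quality, not low PR, so how strongly PR itself will regress is unknown. If selection narrows the baseline spread, k rises above 1 and the gain shrinks.
- The outcome sentence could mean separate comparisons at each visit. The named tests would still be unadjusted.

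None of this favours the fixed coefficient. Apart from one degree of freedom, ANCOVA costs no precision in the cases examined, and it removes the conditional error.

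**Conclusion.** The point holds as one of efficiency. The planned test is valid, but it is usually less precise than an analysis that the collected data already allow. With equal SDs at the two visits, the variance saving is 35%, 25% or 15% at r = 0.3, 0.5 or 0.7. It shrinks as the 3-month SD grows relative to baseline and is nil at a ratio of 1.4 with r = 0.7. The direction is secure; the size is not, because the protocol gives neither r nor the SDs at the two visits.

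The omnibus test has little to gain. The useful gain is in the surgical ALA versus vitamin E contrast. Adjustment does not rescue the non-surgical contrast, which stays at or below about 25% power. The power figures apply to the ANOVA branch. The Kruskal-Wallis branch is equally unadjusted, and planning SDs from 3.96 to 8.90 make it a plausible route. This is a recommended improvement, not a defect that would invalidate the result.

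**What to change.** In Statistical methods {20a}, make the primary between-group analysis an ANCOVA of 3-month PR on randomised group (four levels) with baseline PR as covariate. Use standard errors robust to unequal variances, since the planning SDs differ more than twofold, and check that the named software version provides them. Keep the planned multiplicity correction for the pairwise contrasts. Analyse each continuous secondary outcome in the same way with its own baseline value, and report mean change descriptively.

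The cost is one error degree of freedom and a change of wording, with no added patients, visits or assays. The change should be fixed before anyone sees outcome data by group.

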**Discussion:**

Whether it is necessary to use antioxidants in varicocele-related male infertility, how potent antioxidants should be used, postoperative application or non-surgical independent application still needs to be explored. This study attempts to compare the effects of two antioxidants (ALA and vitamin E) on sperm quality in patients with varicocele-related male infertility (surgical or non-surgical) and attempted to answer the above questions.

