However, ROS generated by OS is undoubtedly an important pathogenic factor in the entire varicocele process, affecting spermatogenesis through multiple pathways and mechanisms [20]. Especially for infertility caused by moderate-to-severe varicocele, whether it is necessary to use antioxidants, how potent antioxidants should be used, postoperative application, or non-surgical independent application still needs to be explored. Alpha-lipoic acid (ALA), chemically named 1,2-dithiolane-3-pentanoic acid, is an 8-carbon, cyclic disulfide antioxidant with the formula C_8_H_14_O_2_S_2_ and molecular weight 206.33 g/mol, which represents a promising antioxidant in the field of female and male infertility that inhibits oxygen-free radicals and rejuvenates oxidized antioxidants (i.e., glutathione and vitamins C and E) [21], as well as promotes the function of enzymes with antioxidant function. Animal experimental studies have shown that ALA can reduce the negative side effects of elevated testicular temperature and reduce OS in varicose rats [22]. It has also been clinically confirmed that ALA or ALA compound antioxidants can improve sperm motility and reduce sperm DNA damage in patients with varicocele after surgery [23, 24]. However, what role does ALA play in varicocele-related male infertility, and can it improve sperm quality more than traditional antioxidants? This is also a problem we think about and try to solve to help us formulate a more optimized treatment plan for varicocele-related male infertility.

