### Objectives {7}

The general objective is to determine the efficacy and significance of ALA in varicocele-related male infertility through a randomized controlled clinical trial.

The specific objective is to determine the effect of different intensities of antioxidant conservative and surgical treatment of varicocele on sperm quality of varicocele-related male infertility patients by comparing surgical and non-surgical supplementation of ALA or vitamin E.

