### Trial design {8}

This is a single-center, randomized, controlled, non-commercial clinical superiority trial evaluating the effectiveness of alpha-lipoic acid on sperm quality in patients with varicocele-related male infertility. The eligible participants will be allocated randomly into the non-surgical observation group, non-surgical control group, surgical observation group, or surgical control group in a ratio of 1:1:1:1. The four groups will be intervened for 3 months and followed up for 6 months. The flow chart is shown in Fig 1.

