Some animal experiments have shown that ALA supplementation can alleviate ROS, reduce testicular tissue damage, and improve testicular spermatogenesis and steroidogenesis disorders [33–36]. A small number of clinical studies have also found that ALA supplementation can improve the quality of semen parameters in male infertility [37, 38], and there are also fewer studies on the application of ALA in varicocele-related male infertility [23, 24]. Previous studies have mostly focused on surgical treatment of varicocele-related male infertility or postoperative supplementation with antioxidants, while this clinical trial intends to study both surgical and non-surgical treatment of varicocele-related male infertility patients and compare the effects of two antioxidants (ALA vs. vitamin E) on semen parameters, seminal plasma MDA and TAC before and after treatment, so as to reveal whether antioxidant use is necessary for varicocele-related male infertility, how potent should be used, non-surgical application, or postoperative application. Since our study involved surgical and non-surgical treatment options, some non-surgical patients are likely to choose further treatment options (varicocelectomy) after finishing the trial, which is also what we may recommend and according to the patient’s wishes. We may continue to follow up these patients who underwent surgery after antioxidant treatment.

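### The trial is a randomised 2x2 that asks about treatment setting, but the planned one-way analysis never estimates whether the ALA-versus-vitamin E difference depends on surgery

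*Protocol article*

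**What the plan says.** **The question.** The abstract's Discussion paragraph says that "postoperative application or non-surgical independent application still needs to be explored" and that the study attempts an answer. Background and rationale {6a} poses the same question. The main Discussion lists, among the things the trial should reveal, "non-surgical application, or postoperative application". Objectives {7} plans to reach the specific objective "by comparing surgical and non-surgical supplementation of ALA or vitamin E".

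**The design.** Trial design {8} randomises to the "non-surgical observation group, non-surgical control group, surgical observation group, or surgical control group in a ratio of 1:1:1:1". With the regimens in Intervention description {11a}, this is a 2x2 layout: surgery yes or no, by ALA or vitamin E. The primary outcome is change in semen parameters at 3 months, chiefly PR.

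**The analysis.** Statistical methods {20a} says that normally distributed, equal-variance data "will be analyzed with one-way analysis of variance, and if the result is statistically significant, multiple comparisons will be performed with Bonferroni correction". Otherwise it uses a Kruskal-Wallis test followed by Holm-corrected pairwise tests. Within-group before-after tests are added. Section {20b} plans no subgroup analyses. No two-way model, interaction term or contrast between the two drug effects appears.

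**The concern.** With vitamin E as the only comparator, the randomised evidence on whether ALA's relative benefit depends on setting is a difference of differences: ALA minus vitamin E in operated men, less ALA minus vitamin E in non-operated men. The stated analysis gives a p-value for each of these two pairs but never compares them.

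A reader who wants a setting conclusion about ALA against vitamin E may then fall back on which pair reached significance. That inference has no controlled error rate. Each pair has modest power after correction over six comparisons, so one pair will often miss by chance although the underlying effects are equal. Significance after surgery without significance in non-operated men could then be taken as evidence that ALA helps more after surgery, when the data may not support it.

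**Working it through.** **Inputs** (Sample size {14}, change in PR, mean and SD)

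| | ALA | Vitamin E | ALA minus vitamin E |
|---|---|---|---|
| Surgical | 12.05 (3.96) | 6.56 (8.90) | 5.49 |
| Non-surgical | 4.15 (8.68) | 1.42 (7.60) | 2.73 |

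Alpha is 0.05 and power 80%, with 16 per arm, or 20 after a 20% dropout allowance.

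**Step 1: reproduce the plan's sample size.** The grand mean is 6.045 and the squared deviations of the four means sum to 61.31. For a one-way F test the noncentrality is n × 61.31 / SD². With the largest stated SD, 8.90, and n = 16 this is 16 × 61.31 / 79.21 = 12.4, giving power 0.826; n = 15 gives 0.797. So 16 is reproduced, and 16 / 0.8 = 20. The calculation powers the four-group omnibus test and says nothing about the drug-by-surgery contrast.

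**Step 2: what each comparison contains.** The planned drug-by-surgery difference is 5.49 − 2.73 = 2.76. The planned pair surgical ALA versus non-surgical ALA is 12.05 − 4.15 = 7.90. This equals 5.14 (surgery effect under vitamin E, 6.56 − 1.42) plus 2.76, so most of it is surgery effect.

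**Step 3: split results when the ALA effect is truly equal.** The rule was simulated as written: F test at 0.05, then pooled-error pairwise tests with Bonferroni over six pairs. The surgery effect was 6.52, the average of 7.90 and 5.14. The equal ALA effect was set to 2.73, to 5.49, or to their average, 4.11. Share of trials with exactly one of the two ALA-versus-vitamin E pairs significant:

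| Equal ALA effect | Stated SDs, 20 per arm | Stated SDs, 16 | SD 8.90, 20 per arm | SD 8.90, 16 |
|---|---|---|---|---|
| 2.73 | 12% | 10% | 9% | 7% |
| 4.11 | 27–28% | 22% | 20% | 15–16% |
| 5.49 | 44% | 37–38% | 35% | 27–28% |

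The interaction test is significant in about 5% throughout. At 20 per arm with the stated SDs and an effect of 5.49, the share is also 44% by the Kruskal-Wallis/Holm route (rank-sum tests between independent arms) and with routing by Levene's test. The result does not hinge on the branch taken.

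**Step 4: precision of the missing contrast.** SE = √(sum of the four variances / n). The stated variances sum to 15.68 + 79.21 + 75.34 + 57.76 = 227.99; with a common SD of 8.90 the sum is 4 × 79.21 = 316.84.

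| | SE | 95% half-width | Power for 2.76 |
|---|---|---|---|
| Stated SDs, 20 per arm | 3.38 | 6.7 | 13% |
| Stated SDs, 16 per arm | 3.77 | 7.5 | 11% |
| SD 8.90, 20 per arm | 3.98 | 7.9 | about 10% |
| SD 8.90, 16 per arm | 4.45 | 8.9 | 9% |

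About 236 per arm would be needed for 80% power (common SD 7.55, the root mean square of the stated SDs).

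**The case against.** Several stronger readings are tempting, and the documents do not support them.

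- **That the protocol asks where ALA should be used.** The setting question is put for antioxidants in general. The question specific to ALA in {6a} is whether it beats traditional antioxidants, and Objectives {7} can be read as comparing four regimens. The point therefore rests on the 2x2 design and the general setting question. Because no arm goes without an antioxidant, even the right contrast speaks only to ALA relative to vitamin E.
- **That the plan will return conflicting verdicts.** Section {20a} contains no rule that significance in one pair means use in that setting alone. The split results measure the risk of a foreseeable misreading. One significant and one non-significant pair are also not effects in opposite directions.
- **That the two drug pairs are the only planned route to a setting answer.** The six pairs include surgical against non-surgical ALA, which is significant in about 75% of simulated trials at the planning means with 20 per arm and the stated SDs. On a four-regimen reading this is a legitimate answer to which regimen does better. It does not replace the contrast, because it also carries the surgery effect (Step 2).
- **That 44% is the figure, or a ceiling.** It is the top of the grid and needs a 5.49-point effect in both settings, whereas {14} assumes 2.73 without surgery. The share peaks near 48% at about 6.5 points, outside the protocol's assumed drug effects.

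It can also be said that an analysis plan could add such a contrast without contradicting {20a}, and that the contrast has little power. Both are true. But {20a} fixes an analysis that ignores the factorial structure, so this is a poorly matched stated method and not merely omitted detail. Low power is a reason to show the interval.

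**Conclusion.** The concern holds in limited form. The stated analysis never estimates whether the ALA-minus-vitamin E difference depends on surgery, although the trial randomises the 2x2 layout that would allow it and sets itself a question about setting. Inferring setting dependence from which pair is significant would mislead in about 7% to 44% of trials if ALA's effect were truly equal, against 5% for a direct test.

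The range assumes normally distributed changes, a surgery effect of 6.52 points, correction over all six pairs, and the effects, SDs and arm sizes in the working. The trial cannot settle the matter at its planned size, with or without the change. What the change gives is a valid estimate that shows its own uncertainty. The point merits a correction to the analysis section but does not undermine the trial's overall comparison of the four arms.

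**What to change.** Add to Statistical methods {20a}, for change in PR, the contrast (surgical ALA minus surgical vitamin E) minus (non-surgical ALA minus non-surgical vitamin E), with its 95% CI. State that any claim that ALA's advantage over vitamin E differs by setting rests on this contrast and not on which pair is significant.

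State the limits alongside it: the expected half-width is about 7 to 9 PR points against a planned difference of 2.76; a non-significant result is not evidence of equal effects; and the contrast does not show whether antioxidants as such are needed in either setting.

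The cost is a few lines of text and one contrast from data already being collected, with no extra patients or visits. The price for the sponsor is to concede in advance that this question will get an imprecise estimate.

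### The ANOVA branch uses plain Bonferroni while the Kruskal-Wallis branch uses Holm; using Holm in both would gain a little power at the same 5% familywise level

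*Protocol article*

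**What the plan says.** In the protocol article, Statistical methods {20a}, Shapiro-Wilk and Levene tests decide how each continuous outcome is analysed. If the data pass both, the four groups are compared by one-way ANOVA and, if that is significant, "multiple comparisons will be performed with Bonferroni correction". If they fail either, a Kruskal-Wallis test is used, and its follow-up comparisons come "with a Holm-Bonferroni method correction for multiple comparisons". The section does not explain the difference, and it does not say which pairs, or how many, are compared.

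Sample size {14} rests on the overall comparison of four means: "Sample size estimation uses a completely random design to compare multiple sample means". It uses "the type I error *α* = 0.05" and is planned "with 80% test power".

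**The concern.** The same follow-up step gets a different multiplicity correction according to the outcome of a pre-test. Holm's step-down procedure holds the familywise error at the same level as Bonferroni under any dependence between the tests, and it rejects every hypothesis that Bonferroni rejects. The protocol already accepts Holm in one branch, so it has no evident objection to the method.

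The follow-up comparisons matter here because the objective is ALA against vitamin E, with and without surgery. A significant four-group F test could reflect surgery alone. Between groups, the antioxidant question is therefore answered only by the corrected pairwise tests, and the trial was not sized for those.

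**Working it through.** **Inputs, all from Sample size {14}.** Changes in progressive motility:
- Surgical ALA: "changes in PR sperm mean value in the surgical observation group was 12.05, and the standard deviation was 3.96".
- Surgical vitamin E: "changes in PR sperm mean value in the surgical control group was 6.56, and the standard deviation was 8.90".
- Non-surgical ALA: "changes of PR sperm mean value in the non-surgical observation group was 4.15, and the standard deviation was 8.68".
- Non-surgical vitamin E: mean 1.42, SD 7.60.
- 16 per group before dropout, 20 after.

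**Assumptions, not in the document.** All six pairs form the family; tests are two-sided; data are normal; pairwise t tests use the pooled ANOVA error.

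**Step 1: reproduce the stated sample size.** The grand mean is (12.05 + 6.56 + 4.15 + 1.42)/4 = 6.045. The sum of squared deviations is 36.06 + 0.27 + 3.59 + 21.39 = 61.31. The noncentrality is n × 61.31/SD². With the largest SD (8.90) and n = 16 it is 16 × 61.31/79.21 = 12.4, which gives power 0.826; n = 15 gives 0.797. So 16 per group is reproduced, and 16/(1 − 0.20) = 20. This is power for the overall F test, not for any pair.

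**Step 2: the two rules.** Bonferroni tests every p-value at 0.05/6 = 0.0083. Holm orders the p-values and tests them at 0.05/6, 0.05/5, 0.05/4, 0.05/3, 0.05/2 and 0.05, stopping at the first failure. The first threshold is the same and the later ones are larger, so Holm cannot lose a rejection.

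**Step 3: power if every trial goes to ANOVA** (200,000 simulated trials per scenario, pairs tested only after a significant F test). The common SD is √[(3.96² + 8.90² + 8.68² + 7.60²)/4] = 7.55.

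| n per group | SDs | Surgical pair, Bonferroni → Holm | Non-surgical pair, Bonferroni → Holm |
|---|---|---|---|
| 16 | common 7.55 | 26.1% → 31.4% | 5.0% → 7.3% |
| 16 | as planned | 24.4% → 29.7% | 6.5% → 8.8% |
| 20 | common 7.55 | 34.9% → 41.8% | 6.3% → 9.7% |
| 20 | as planned | 33.6% → 40.9% | 8.1% → 11.5% |

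Holm rejected everything that Bonferroni rejected in every trial. The chance of at least one significant pair is the same under both (96.9% at n = 20, common SD).

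**Step 4: apply the plan's own pre-tests.** The choice of correction matters only in trials that reach the ANOVA branch.
- Planning SDs: Levene's test alone rejects in about 67% of trials at n = 16 and 80% at n = 20. With Shapiro-Wilk added, the ANOVA branch is reached in about 26% and 16%. Over all trials at n = 20 the gain is about 1.4 points (surgical) and 0.7 points (non-surgical).
- Common SD 7.55: the branch is reached in about 76% of trials at n = 20, and the gain is about 5 and 2.6 points.

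**Step 5: a smaller family.** If only the two ALA-versus-vitamin-E pairs are tested, without a preceding F test, at n = 20 and common SD, the surgical pair goes from 50.8% to 52.3% (+1.5 points) and the non-surgical pair from 13.1% to 16.7% (+3.6 points).

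**Step 6: familywise error** (n = 20, common SD, after a significant F test).

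| True means | Bonferroni | Holm |
|---|---|---|
| all equal | 3.8% | 3.8% |
| 10, 10, 0, 0 | 1.7% | 4.2% |
| 10, 0, 0, 0 | 2.2% | 4.0% |
| 20, 10, 0, 0 | 0.8% | 4.5% |

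Both stay below 5% throughout.

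**The case against.** The strongest reply is that nothing here is wrong. Bonferroni after a significant ANOVA is valid, the two branches use different tests, and no rule requires them to share a correction. That stands: this is a matter of efficiency and consistency only.

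A reader might take the 7-point gain as what the trial would gain on its primary outcome. The documents do not support that. The planning SDs run from 3.96 to 8.90, and data like these usually fail the variance pre-test and go to the branch that already uses Holm. The 7 points apply only if every trial reaches ANOVA. The branch still matters, because the same rule governs the other continuous outcomes, including hormones, testicular volume, DFI, MDA and TAC.

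A reader might also infer that Bonferroni buys nothing at all. That goes too far. It bounds the expected number of false rejections at 0.05, which Holm does not; its realised familywise error is lower when some groups differ (Step 6); and it has matching simultaneous intervals. None of this is a stronger familywise guarantee, and the statistical section does not call for simultaneous intervals.

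Finally, a reader might expect the change to make the result independent of the pre-tests, or to rescue the pairwise comparisons. It does neither. The pre-tests would still choose between the parametric and rank tests. Even in the more favourable case where every trial goes to ANOVA, power at n = 20 stays near 41% to 42% (surgical) and 10% to 12% (non-surgical).

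**Conclusion.** The point holds as a minor one. The protocol fixes two different corrections for the same step without a reason, and the one in the ANOVA branch is never more powerful than the other at the same familywise level. For the primary outcome at 20 per group, the overall gain from using Holm lies between about 1.4 points (planning SDs) and 5 points (common SD 7.55) for the surgical pair, and between about 0.7 and 2.6 points for the non-surgical pair. These figures assume six two-sided pairs and normal data. The number of pairs is not stated, and a two-pair family gives about 1.5 and 3.6 points instead. No conclusion drawn with plain Bonferroni would be invalid.

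**What to change.** In Statistical methods {20a}, replace Bonferroni with Holm-Bonferroni in the sentence on comparisons after ANOVA, so that both branches use the same procedure. Make the change before the data are analysed.

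The cost is one word in the text and simple arithmetic on the raw p-values. Design, sample size and data collection are unchanged. The one drawback is that Holm has no simple matching simultaneous confidence intervals. Bonferroni intervals can still be reported beside the Holm-adjusted p-values, with a note that the two may occasionally disagree.
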